# Effects of weight management program on postural stability and neuromuscular function among obese children: study protocol for a randomized controlled trial

**DOI:** 10.1186/s13063-015-0673-6

**Published:** 2015-04-10

**Keywords:** Childhood obesity, Neuromuscular function, Postural stability, Randomized controlled trial, Weight loss

## Abstract

**Background:**

Childhood obesity is one of the most critical public health problems in the world. It is associated with low neuromuscular function and postural deformities. Whether weight loss can improve postural stability and neuromuscular control, benefit daily activities, or prevent injury is unknown. Therefore, this study attempts to investigate the effect of a 6 month weight management program on postural stability and neuromuscular control among obese children.

**Methods/design:**

We will conduct a prospective, single-blind, randomized controlled trial with 120 prepubescent obese children. Participants will be randomly assigned to a weight management group or a control group. The weight management group will participate in a dietary and exercise program. The control group will receive health education. After the intervention, participants will be followed for 6 months with no active intervention. The primary and secondary outcomes will be assessed at the baseline, and after 6 months and 12 months. Primary outcome measures will include body weight, body height, body mass index, waist circumference, hip circumference, and body fat percentage. Secondary outcome measures will include three-dimensional functional biomechanics in different tasks, proprioception tests of the knee and ankle, neuromuscular response of the leg muscles, and muscle strength tests of the knee and ankle. Furthermore, adverse events will be recorded and analyzed. An intention-to-treat analysis will be performed if any participants withdraw from the trial.

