## Methods/design

### Study design

The study design is a single-blind randomized controlled trial that will compare a weight management program with health education. This study will be conducted at the Sport Medicine and Rehabilitation Center, Shanghai University of Sport. A total of 120 prepubescent obese children aged 8 to 10 years old will be included in the study. All participants will be recruited from a local primary school in Yangpu District, Shanghai, China. A multidisciplinary team composed of clinicians, dietitians, and exercise specialists will run the program.

Prior to initiation of the study, all subjects will complete a questionnaire that asks for details, such as medical history. The subjects will also complete the Mini-Mental State examination and Activity of Daily Living test, and describe their exercise habits (frequency and duration). Informed consent will be requested from all subjects and their parents prior to their inclusion in this study.

Participants who meet the inclusion criteria will be allocated in a 1:1 ratio by computer-generated randomization. After randomization, participants will be assigned to either the weight loss group or a health education group (control). This study will include assessments at the following time points: before intervention, after an intervention period of 6 months, and after a further follow-up period of 6 months with no active intervention. The total study period will be 12 months.

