#### Primary outcome measures

##### Anthropometric measurements

Body weight and height will be measured with each study participant in minimal clothing and bare feet. Body height will be measured to the nearest 0.5 cm using a fixed stadiometer (Holtain Ltd., Crymych, Dyfed, UK). Body weight will be measured to the nearest 0.1 kg using a standard scale (TBF 543 model; Tanita, Tokyo, Japan). Body mass index will be calculated as:$$ \mathrm{Body}\ \mathrm{m}\mathrm{ass}\ \mathrm{in}\mathrm{dex}=\frac{\mathrm{Body}\ \mathrm{weight}\ \mathrm{in}\ \mathrm{kg}}{{\left(\mathrm{Body}\ \mathrm{height}\ \mathrm{in}\ \mathrm{m}\right)}^2} $$

Waist circumference will be recorded to the nearest 1 mm and measured at the midpoint between the lowest rib and the superior border of the iliac crest using an inelastic measuring tape [32]. Hip circumference will be measured at the maximum posterior extension of the buttocks [32].

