**Flow diagram of study design.**

### Statistical analysis

Statistical analysis will be performed using SPSS for Windows version 17.0 (SPSS Inc. Chicago, IL). Data will be presented as the mean and standard deviation in which the distribution of variables is normal. Potential covariates will be determined at the baseline (that is, weight status, growth potential, sex, age, and socioeconomic status), and the difference by study groups or sex will be determined using one- or two-way analysis of variance or *χ*^2^ test. Baseline differences between those who attend and those who do not attend the follow-up measurements will be examined using separate variance *t* tests.

Intention-to-treat analysis will be performed by including all participants in the analysis according to the original group allocation. The follow-up will be maximized regardless of program attendance. A linear mixed model, which includes time (as a repeated factor), group, their interaction, and Bonferroni correction for *post-hoc* multiple comparisons, will be used to determine whether a significant time by group effect exists at the baseline, and after 6 months and 12 months. Average intervention effects of the follow-up period will be estimated and tested using the Bonferroni method for *post-hoc* analysis, in which groups by time interactions are insignificant.

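### Six primary outcomes, one of them body height, with none singled out and no error control across them

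*Protocol article*

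**What the plan says.** The abstract (Methods/design) states that "Primary outcome measures will include body weight, body height, body mass index, waist circumference, hip circumference, and body fat percentage". In the body of the article, the section on primary outcome measures covers the same six variables under its anthropometric and body fat subsections. On timing, the abstract says that "The primary and secondary outcomes will be assessed at the baseline, and after 6 months and 12 months".

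Height has its own measurement rule ("Body height will be measured to the nearest 0.5 cm using a fixed stadiometer"). It then enters the formula introduced by "Body mass index will be calculated as", where weight is divided by height squared.

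The Statistical analysis section describes the model as follows: "A linear mixed model, which includes time (as a repeated factor), group, their interaction, and Bonferroni correction for" multiple comparisons made post hoc. The model "will be used to determine whether a significant time by group effect exists at the baseline, and after 6 months and 12 months". Where the interaction is not significant, a second step applies: "Average intervention effects of the follow-up period will be estimated and tested using the Bonferroni method for" post-hoc analysis.

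The Study design section gives the size as "A total of 120 prepubescent obese children aged 8 to 10 years old will be included in the study", allocated 1:1, so 60 per arm.

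**The concern.** The article publishes a primary list of six and commits to multiplicity control at one level only, among comparisons within a single outcome's model. A trial run this way has six routes to a primary finding, and nothing in the stated plan holds the overall false-positive rate at the level used for each.

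Height is a separate problem. A weight programme has no stated reason to change height, and the article does not say whether a taller or shorter intervention group would be a benefit. Because it carries the primary label, a chance difference in height could be reported as a primary result. It is also counted twice: once alone, and once through BMI, which is computed from two other members of the list.

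**Working it through.** The article gives no error rate or power calculation, so there is no stated figure to reproduce.

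**Inputs from the article**
- Primary outcomes: 6 (abstract; primary outcome sections).
- Main test: one time-by-group interaction per outcome over baseline, 6 and 12 months (Statistical analysis).
- Sample: 120 in total, 1:1, so 60 per arm (Study design).

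**Assumptions, not in the article**
- Two-sided 0.05 per outcome.
- Correlation between outcomes from 0 to 0.9.
- Correlation between visits of 0.5 to 0.7, where visits enter the calculation.

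**Step 1: independent outcomes.** P(at least one false positive) = 1 − (1 − 0.05)^6 = 1 − 0.735 = 0.265. Positive correlation lowers this, so for the interaction tests it is a ceiling.

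**Step 2: correlated outcomes.** Multivariate normal simulation under no effect, with one test per outcome at 0.05:

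| Correlation between outcomes | At least one false primary result |
|---|---|
| 0 | 26% |
| 0.5 | 21% |
| 0.7 | 16–17% |
| 0.8 | 14% |
| 0.9 | 11% |
| Five measures at 0.8, height at 0.3 with each | 17% |

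The last row is illustrative. It shows that a weakly related variable such as height adds more to the error than another strongly related one: six outcomes all at 0.8 give 14%.

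**Step 3: the fallback test.** If the interaction is not significant, the average effect is tested. With two groups this is one contrast, so Bonferroni within the model has little or nothing to divide. If both steps are run at 0.05, simulation over three visits raises the error per outcome from 5% to about 7.5% when the average effect is a change from baseline, and to nearly 10% when it is a group mean. The union bound is 0.05 + 0.05 = 10%. Across six outcomes the error becomes 30–37% at correlation 0.5, 20–26% at 0.8 and 16–21% at 0.9. The article does not define the average effect closely enough to choose among these, so they indicate direction and possible size only.

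**Step 4: after correction.** One primary test at 0.05 has 5% error. Bonferroni over six uses 0.05/6 = 0.0083 each and gives 1 − (1 − 0.0083)^6 = 4.9% if independent, 4.1% at correlation 0.5 and 2.8% at 0.8. Dropping height alone leaves five outcomes and a ceiling of 1 − 0.95^5 = 22.6%, so that step is not enough by itself.

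**Step 5: cost in detectable effect.** Two-sample t test, 60 per arm, 80% power:
- level 0.05: 0.516 SD
- level 0.05/5 = 0.01: 0.633 SD
- level 0.05/6 = 0.0083: 0.645 SD

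The last two are worst cases for Holm, which tests later outcomes at less strict levels once the first has been rejected.

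**The case against.** The strongest defence is that this is a journal article. A rule across outcomes, a success criterion and a primary visit may stand in a full protocol or analysis plan that is not shown. That defence stands as far as it goes: their absence alone would be no finding. It does not reach what the article itself fixes, which is a primary list of six that includes height, and a stated multiplicity method that stops inside each model.

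A reader might infer that six outcomes at two visits make 12 tests at full alpha, with 1 − 0.95^12 = 46% error. The documents do not support that. The visits are tested jointly through one interaction per outcome, and comparisons between visits are Bonferroni-corrected. The within-model correction does help: if a claim also required a Bonferroni-significant visit comparison after a significant interaction, the error across six outcomes would be about 15–16% at correlation 0.5, 10–11% at 0.8 and 8% at 0.9. That is lower, but still above 5%.

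Independence is not credible either, since weight, height and BMI are tied by a formula. The 26% is therefore a bound and not an estimate.

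Finally, height may have been listed simply because it is measured alongside weight and feeds BMI. That is plausible, but the abstract names it among the primary outcome measures, so the label has to be corrected where it stands. That a height difference would actually be claimed as success is a possibility the list leaves open, not something the article states.

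**Conclusion.** The point holds. Six primary outcomes are listed without a hierarchy, Bonferroni works only within each outcome's model, and height is primary without a stated direction of benefit. At an assumed two-sided 0.05 for one interaction test per outcome, the chance of at least one false primary result is about 11–21% for correlations of 0.9 down to 0.5, which is roughly two to four times 5%. The fallback test can only raise this. The size depends on a significance level and correlations that the article does not give. The direction does not, short of perfectly correlated outcomes.

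A reader might also infer that body fat percentage at 6 months is the natural single primary. Nothing in the article ranks it above the other measures or ranks 6 months above 12, so that choice is left open here.

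**What to change.** 1. Remove body height from the primary list. Keep it as the BMI input and as a descriptor of growth.
2. Then do one of the following before outcome data are seen:
   - name one primary outcome at one primary visit and make the others secondary; or
   - keep several primaries and apply Holm across them, stating the overall significance level and the test to which it applies.
3. Say whether the average-effect test after a non-significant interaction can support a primary claim. If it can, include it in the error control.

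The choice of measure is the sponsor's. It should be made with the stated aim in view, because postural stability and neuromuscular function are currently secondary outcomes.

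The change is to the wording of the protocol and analysis plan, and of the registry entry if it carries the same list. The article gives the trial status as recruitment, so this may still precede outcome data. The downside is that fewer outcomes carry the primary label. If several are kept, the detectable effect rises from 0.52 SD to at most about 0.63 SD with five, or 0.64 SD if all six were kept. A single primary avoids that loss.

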**Discussion:**

The important features of this trial include the randomization procedures and large sample size. This study attempts to estimate the effect of weight loss intervention on outcomes, including daily life function, postural stability, and neuromuscular control in prepubescent obese children. Therefore, our results can be useful for obese children, medical staff, and healthcare decision makers.

**Trial registration:**

Chinese Clinical Trial Registry ChiCTR-IOB-15005874.

## Background

Childhood obesity is one of the most critical public health challenges of the twenty-first century [1]. Evidence shows that childhood and adolescent obesity are significantly associated with the presence and clustering of cardiovascular risk factors in childhood [2]. Other childhood clinical consequences include asthma, Type 1 diabetes, low-grade systemic inflammation, sleep apnea, and musculoskeletal disorders, particularly of the lower limbs and feet [2,3]. Childhood obesity is also associated with a range of functional problems, including pain, discomfort and joint stiffness (particularly in the lower extremities), lower muscular strength, and postural deformities [4].

Childhood is the most important stage in growth and development. Being overweight or obese during this period can influence movement ability and postural control capacity [4]. Several studies reported the difficulties encountered by overweight and obese people when executing simple activities in daily living, particularly during weight-bearing tasks such as walking and climbing stairs [5,6]. These results suggest a possible link between movement efficiency in the gait cycle and decreased postural stability of obese children [7-11]. Several studies on the postural control of obese children published evidence of alterations in their postural control ability. These studies focused on the postural stability in obese children when walking or standing in different postures. Obese children displayed a longer cycle duration, lower cadence, lower velocity, and longer stance period than normal-weight subjects during walking [7-10]. Obese boys spent a significantly larger percentage of time in the double-support and stance phase than their non-obese counterparts during walking [7,11]. Furthermore, Deforche and colleagues [10] found that obese boys had slower weight transfer, lower rising index, and larger sway velocity in a sit-to-stand test than non-obese boys. The characteristics of the gait pattern indicate a decrease in dynamic postural stability in obese children. The static postural stability in obese children also decreased [9-11]. Previous studies show that static postural stability is lower in obese children than in normal-weight children. McGraw *et al.* [11] examined the sway of center of pressure during standing in obese boys in different vision conditions (that is, full vision, dark, and visual conflict). They found that the maximum displacement of center of pressure and the root mean square of center of pressure displacement in the anterior-posterior and medial-lateral directions tended to be larger for obese boys than for non-obese boys across all conditions. The difference in the measurements in the medial-lateral direction between obese and normal-weight children was most significant. Furthermore, a recent study suggests that obese and normal-weight children use different postural strategies to maintain balance, the consequences of which should be further clarified [12].

Obese children perform poorly in static and dynamic postural control [5]. The larger body size, larger body mass index, abnormal body fat distribution, and potential neuromuscular disadvantage of obese children can contribute to their postural instability [13]. Several studies of obese children provided evidence of this association between body weight or body shape and postural stability [11,14]. Furthermore, postural control is related to the function of vision, vestibular, proprioception, and neuromuscular control. Several studies previously demonstrated that information from some sensory receptors on obese individuals could be associated with postural instability [11,15]. McGraw *et al.* [11] found that visual conflict induced a more significant alternation of static postural performance in obese children than in their normal-weight counterparts. Several researchers reported a reduction in the sensitivity of plantar mechanoreceptors in obese feet [16]. This alteration might contribute to the postural instability in the obese group [4]. Obese children show a deficit in proprioception in knee flexion. Such alterations in their proprioception might be associated with decreased postural control in obese children [15]. Moreover, obese children have less relative strength during isokinetic testing [17]; the majority of deficits are evident where strength is a major prerequisite of functional movement tasks. Specifically, obese children typically perform poorly in measures of muscular strength that require moving the body against gravity [18,19]. Abdominal strength and endurance, functional knee strength, and lower extremity strength, power, and endurance are all low in this population [4].

Weight reduction for obese children is associated with decreased body mass index and body fat, increased physical fitness, and improved movement skills [20,21]. Previous studies found that weight loss in obese adults could improve their postural stability [22,23]. Obese children have worse postural stability and neuromuscular control than normal-weight children. However, only a few studies have examined the influence of weight reduction on postural balance among obese children. Recently, Steinberg *et al.* [24] found that a weight management program could improve static stability and lower potential falling probability of obese participants. However, it is not known whether weight loss interventions influence performance associated with dynamic postural instability and neuromuscular function in obese children.

Maintaining a stable posture is essential for many daily activities and injury prevention. The poor postural stability of obese children might lead to a higher risk of falling and fractures compared with that of normal-weight children [25,26]. In addition, childhood is the most important stage of human growth and development. If weight loss increases postural stability and neuromuscular control at this stage, it will benefit daily activities and help to prevent injuries. Therefore, this study attempts to investigate the effect of a 6 month weight management program on postural stability and neuromuscular control among obese children.

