##### Body fat percentage measurement

Dual-energy X-ray absorptiometry (GE Lunar Prodigy, software version 10.51.006, GE Healthcare, Madison, United States) will be used to measure body fat percentage. Each participant will be scanned in the supine position using X-rays at two energy sources (40 keV and 70 keV) in fast mode. A series of transverse scans will be performed from head to toe at 1 cm intervals. The time spent will be approximately 5 min, depending on the participant’s height.

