These biomechanical data will be collected while each participant performs three tasks:Level walking at normal speed, faster speed, and slow speedNormal cadence is the subject’s preferred speed. Fast speed is 30% faster than the normal walking speed, and slow speed is 10% slower than the normal walking speed [11]. Four force plates will be embedded on the ground in the middle of a walkway, so that the participants can plant their feet on each plate consecutively during walking.Stair climbingThe experimental staircase consists of six steps. The step dimensions are 17 cm (height) and 28 cm (tread) with a stair slope of 31° [33]. No handrail will be used. Three force platforms (9286AA, Kistler Instruments Corp, Switzerland) are embedded in the second, third, and fourth steps of the staircase. The participants will be asked to walk, ascend, and descend at their natural speed without any reference to the force platforms.Rising from a seated positionDuring the task, the participants will rise from a seated position from a 30 cm high bench. They will be instructed to sit on the edge of the bench, with each foot on a force plate equidistant from the center line, and to bend their knees so that their feet are slightly behind their knees [10].Static posture stability will be examined during the double-leg stance and tandem stance with eyes open and closed [11]. The subjects stand with two heels touching together and the feet externally rotated by 10° in the double-leg stance. The subjects stand with the dominant foot forward from heel to toe in the tandem stance. The center of pressure data will be collected from a force platform (9286AA, Kistler Instruments Corp, Switzerland) using BroWare data collection and analysis software with a sampling frequency of 1,000 Hz in a computer workstation. The subjects will be asked to stand as still and as quietly as possible with arms akimbo and barefoot to eliminate the effects of shoes, socks, and heel height. The required standing time is 30 s. If the participant loses balance in the period (steps to regain balance), he or she will be asked to repeat the test up to a maximum of three times. A 3 min rest will be allowed between two tests. The center of pressure displacement in the medial-lateral and anterior-posterior directions will be used to analyze postural stability.

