The strengths of our protocol are as follows: (1) the use of combined physical activity and nutritional intervention in postural stability and neuromuscular function among obese children, which has not been previously described in this population; (2) the relatively long study duration, with an intervention period of 6 months and a follow-up period (with no active intervention) of 6 months, for a total study period of 12 months; (3) extensive follow-up to monitor the effects of the combined physical activity and nutritional intervention on postural stability and neuromuscular function among obese children; (4) evaluation of dynamic and static postural stability using fully three-dimensional biomechanical analysis to determine dynamic postural stability and provide a quantitative analysis of the intervention effect; (5) measurement of the neuromuscular function to provide advanced findings to explain the possible mechanisms of postural instability in obese children; and (6) a comprehensive dissemination plan to ensure the adequate uptake of knowledge generated in this study. However, this study also has several limitations. First, recruitment is limited to prepubescent obese children, and thus the study results may only be valid for prepubescent obese children. The use of a larger sample size will also address the current study’s limitation of relying on a relatively small study population and the fact that it is not a multicenter trial. Moreover, we will not compare the efficacy of the weight loss program with that of other weight loss programs because of the limited subject number.

In conclusion, this study attempts to estimate the effect of weight loss intervention on outcomes, including daily life function, postural stability, and neuromuscular control in prepubescent obese children. The study results may provide evidence to support the beneficial effects of a weight loss management program on postural stability and neuromuscular control, potential vestibular stress or disturbances, and a falling probability of obese children. Further comprehensive research on the weight management program for obese population will be proposed on the basis of the proposed project.

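### The stated question is postural stability and neuromuscular control, but all six primary outcomes are body-size or body-composition measures, so the primary result cannot answer it

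*Protocol article*

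**What the plan says.** The title announces "Effects of weight management program on postural stability and neuromuscular function among obese children". The Background closes on the aim: "this study attempts to investigate the effect of a 6 month weight management program on postural stability and neuromuscular control among obese children". The Abstract repeats that aim, and the Discussion opens and concludes on the same subject, adding daily life function.

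The outcome tiers are set in the Abstract and repeated under Outcome measures. On the primary tier: "Primary outcome measures will include body weight, body height, body mass index, waist circumference, hip circumference, and body fat percentage". The first five are measured under Anthropometric measurements. The sixth has its own subheading, where dual-energy X-ray absorptiometry "will be used to measure body fat percentage". On the other tier: "Secondary outcome measures will include three-dimensional functional biomechanics in different tasks", followed by proprioception, neuromuscular response and muscle strength.

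For static stance, the section on postural stability assessment says: "The center of pressure displacement in the medial-lateral and anterior-posterior directions will be used to analyze postural stability". The Statistical analysis section plans a linear mixed model with time, group and their interaction, and Bonferroni correction for post-hoc comparisons. It singles out no outcome.

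The Discussion ends by saying that the results may also support benefits on "potential vestibular stress or disturbances, and a falling probability of obese children".

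**The concern.** The primary outcome should carry the trial's main conclusion. Here the main question and the primary tier do not meet. A positive primary result would show that the programme changes body size or fat. It would not show that children stand, walk or react better. A null primary result would not settle the matter either, because an exercise programme could affect strength or balance without a detectable change in body mass.

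The Background makes the gap wider. It presents weight reduction in obese children as already associated with lower body mass index and body fat, and it reports a recent study in which a weight management programme improved static stability. It names dynamic postural instability and neuromuscular function as what is not yet known. The primary tier therefore tests what the authors treat as largely established, and the unknown is left to the secondary tier.

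At stake is what the trial may claim. If the plan is followed as written, its headline conclusion on stability would be drawn from a long list of secondary variables, none of which is marked in the article as carrying the main question.

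**Working it through.** **1. Objective against primary outcomes.**

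| Primary outcome | What it measures | Stability or neuromuscular? |
|---|---|---|
| Body weight | body size | no |
| Body height | body size | no |
| Body mass index | body size | no |
| Waist circumference | body size | no |
| Hip circumference | body size | no |
| Body fat percentage | body composition | no |

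The score is 0 of 6. Everything under Secondary outcome measures (posture, proprioception, electromyography, strength) bears on the objective. No section gives weight or body composition as the objective, and none explains their primary status, for example as a check that the programme worked or as a mediator.

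**2. Size of the secondary set that carries the question.** This is a minimum count from the Secondary outcome measures section:

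- static stance: 2 stances × 2 vision conditions × 2 directions = 8
- proprioception: 2 joints × 2 directions = 4
- onset latency: 5 muscles = 5
- electromyography in tasks: 8 muscles × 2 measures (amplitude, timing) × 2 tasks = 32
- strength and endurance: knee peak torque 2, knee endurance index 2, ankle peak torque 2, ankle relative torque 2 = 8

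Total: 8 + 4 + 5 + 32 + 8 = 57. Walking is counted as one task although three speeds are planned, and no three-dimensional kinematic or kinetic variable is included, so 57 is low.

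Assume one test per variable at 0.05 with all null hypotheses true:

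- expected false positives = 57 × 0.05 = 2.85, whatever the correlation
- chance of at least one = 1 − 0.95^57 = 0.946 if the tests are independent, and lower if they are positively correlated

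**3. What the planned size could detect on one stability variable.** The article gives 120 children allocated 1:1, hence 60 per arm. It gives no standard deviation or expected effect for any stability variable, so this step is an illustration. It assumes a two-sided 0.05 test of two means, with detectable difference in SD units = (1.96 + z_power) × √(2/n).

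| Children per arm | 80% power | 90% power |
|---|---|---|
| 60 (no loss) | 0.51 SD | 0.59 SD |
| 48 (assumed 20% loss) | 0.57 SD | 0.66 SD |

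One stability variable could therefore serve as primary at the planned size if an effect of about half a standard deviation is plausible. The documents do not show whether it is.

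**4. Closing statements against measured outcomes.** The outcome sections define no vestibular test and no falls endpoint. The Abstract says adverse events will be recorded, but that is not a defined falls outcome.

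**The case against.** The strongest reply is that nothing is lost. The stability and neuromuscular outcomes are to be assessed at baseline, 6 months and 12 months like the primary ones, the analysis follows the original allocation, and the article ties no sample size, alpha or model to the primary label. On this view the mismatch is one of labels. Part of this stands. A reader might infer that the trial cannot answer its question at all, and the article does not support that, because the secondary analyses can inform it. What remains is that the primary result cannot answer it, and the primary label governs which finding is confirmatory.

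A reader might also infer that the plan runs 57 uncorrected tests at each visit, with a 95% chance of a false positive. The article does not say so. It plans one time-by-group model per variable over all visits, with Bonferroni correction of the post-hoc comparisons. What it does not state is a correction across outcomes. The 95% is the independence case, and measures on the same muscles or the same stance are surely correlated. A ranking of secondary outcomes may also sit in an analysis plan that is not shown, so its absence from the article is not a fault. The count is supporting context only.

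A third tempting step is to name medial-lateral sway in tandem stance as the obvious primary, because the Background says of earlier work: "The difference in the measurements in the medial-lateral direction between obese and normal-weight children was most significant". That remark comes from a comparison of obese with non-obese boys, not from response to weight loss, and the Background does not link it to tandem stance. The variable is also static, whereas the stated gap is dynamic stability and neuromuscular function. Nor is it fully defined: the Background distinguishes maximum from root mean square displacement, and the assessment section chooses neither.

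Finally, the vestibular and falls wording is hedged discussion text and fixes no analysis. That is right, and it is a minor point.

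**Conclusion.** The point holds. The article itself states both the objective and the two outcome tiers, so the mismatch is not a product of condensation, and an unseen analysis plan would not remove it from the text. None of the six primary outcomes addresses the stated question. The primary result, positive or null, therefore leaves that question open.

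This rests on reading the text and needs no numerical assumption. The supporting figures do: about 2.9 expected false positives and a chance of at most about 95% of at least one assume 57 variables, one test each at 0.05, all null hypotheses true, and independent or positively correlated tests. The verdict does not depend on them, and it does not extend to saying that the trial lacks error control or collects the wrong data.

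**What to change.** Either of two changes would align the plan.

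1. **Realign the primary outcome.** Make one postural-stability or neuromuscular variable that is already measured primary. Before outcome data are seen, specify the task or stance, the vision condition and direction where they apply, the summary statistic and the time point (for example 6 months). Choose it to match the gap named in the Background, or explain why a static measure is used. State what effect 120 children can detect on it. Move weight and body-composition measures to secondary, as evidence that the programme worked.
2. **Realign the objective.** Keep the present primary outcomes, restate the primary objective as weight and body composition, and present stability and neuromuscular findings as secondary or exploratory in the conclusion.

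Under either option, remove or limit the closing statements on vestibular disturbance and falling probability.

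The cost is a protocol amendment, with the registry entry updated if it lists the same outcomes (it is not shown here). The article gives the trial status as recruitment. No new measurement is needed. Under option 1 the weight outcomes lose primary status, and the sponsor must find a standard deviation and a plausible effect for the new primary. Under option 2 the headline claim narrows.
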